### Outcomes and measures

2.6

#### Primary outcomes

2.6.1

The primary outcome is the proportion of participants having an improvement at week 8, which includes the response per HAMD-17 defined as a ≥ 50% reduction from the baseline^[41]^ or clinical recovery (score ≤ 7).^[21]^

#### Secondary outcomes

2.6.2

The proportions of participants achieve an improvement in neurological function at weeks 4 and 8 during the trial. The improvement will be decided by a reduction of ≥ 50% or the total score of 0–1 in the National Institute of Health Stroke Scale (NIHSS) score (ranging from 0 to 42, higher scores indicate a more severe neurological deficit).^[42]^

The proportions of participants achieve an improvement in independence at weeks 4 and 8, as measured by a modified Rankin Scale (mRS) over the trial (scores on this scale range from 0 to 6, with higher scores indicating more significant disability),^[43]^ and the improvement is defined as 0, 1, and 2 in mRS.

The proportions of participants with a Barthel Index (BI) score of ≥90 at weeks 4 and 8 during the study. The BI is used to assess the activities of daily living (ranging from 0 to 100, higher scores indicate increased independence).^[44]^

The proportions of participants have improvements in the Clinical Global Impression scale (CGI). The CGI includes the severity scale (CGI-S) and the improvement scale (CGI-I), both are 7-point rated scales, with lower scores indicating less illness and more improvement, respectively.^[45]^

The changes of participants on anxiety symptoms at weeks 4 and 8 assessed by the Hamilton Anxiety Rating Scale (HAMA), and it ranges from 0 to 56, and higher scores indicate more anxiety.^[46]^

The changes of participants on cognitive function at weeks 4 and 8, as evaluated by the Mini-Mental State Examination (MMSE) (range from 0 to 30, higher scores indicate impaired cognition)^[47]^ and the Montreal Cognitive Assessment (MoCA) (ranging from 0 to 30, and higher scores indicate impaired cognition in different cognitive domains).^[48]^

The changes of beta-and gamma-oscillations at weeks 4 and 8, as assessed via resting-state high-density electroencephalogram (rsHEEG) by utilizing a 128 channel electroencephalogram (EEG) system (Geodesic EEG system 400, Electrical Geodesics, Inc., OR) at baseline, week 4, and week 8. Gamma and beta-oscillations induced by tACS correlate with aspects of executive function and emotional regulation.^[49,50]^

The variations of cognitive status at weeks 4 and 8, as measured by the repeatable battery for the assessment of neuropsychological status (RBANS), which includes different domains of attention, immediate and delayed memory, language, and visuospatial/constructional. And the Chinese version of RBANS has been certified as a reliable tool for cognitive function assessment with reasonable reliability and validity.^[51]^ The higher scores indicate the better in the neurocognitive state.

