### Inclusion and exclusion criteria

2.3

A diagnosis of PSD is based on the “Depressive disorder due to another medical condition” of Diagnostic and Statistical Manual of Mental Disorders, Fifth Edition (DSM-V).^[39]^ Inclusion criteria are as follows: aged 18 to 70 years of either sex, right-handed, more than 6 months after the onset of stroke; satisfying with the criteria of major depressive disorder with single episode,^[39]^ the duration of depressive disorder persists for more than two weeks; having the Hamilton Depression Rating Scale 17-Item (HAMD-17) scores higher than 17 at baseline;^[40]^ absence of psychiatric disorder or family history of psychosis before stroke; has never taken antidepressants before enrollment; having the level of audiovisual for examinations required for the study, and providing signed informed consent.

Exclusion criteria include: patients with life expectancy < 6 months; severe or unstable organic diseases, acute brain injury and infection; the impaired skin integrity at the electrode placement site or skin allergic to electrode gel or adhesive; active current suicidal intent or plan as shown by a score of ≥3 on the suicide item of HAMD-17; current participation in any other clinical trial; prior exposure to all kinds of neuromodulation treatments (including electroconvulsive therapy, TMS, tDCS, etc); prior exposure to any implanted device in body (including a cochlear implant, cardiac pacemaker, an implanted device or metal in the brain); a history of brain organic diseases (including seizures, hydrocephalus, and brain tumors), and any situations the investigators believe that they are not suitable for this study.

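### Improvement in mRS, and one of the two routes to improvement in NIHSS, is a fixed score level that participants may already hold at baseline, so unchanged or worsened participants can count as improved

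*Protocol article*

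**What the plan says.** Section 2.6.2 of the protocol article sets three functional outcomes at weeks 4 and 8:

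- **mRS.** The outcome is introduced as improvement in independence, and "the improvement is defined as 0, 1, and 2 in mRS". Baseline plays no part.
- **NIHSS.** Improvement in neurological function has two routes: "The improvement will be decided by a reduction of ≥ 50% or the total score of 0–1". The first refers to baseline; the second does not.
- **Barthel Index (BI).** "The proportions of participants with a Barthel Index (BI) score of ≥90 at weeks 4 and 8 during the study". This is also a level, but the text does not call it improvement.

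Section 2.3 places participants "more than 6 months after the onset of stroke" and limits the severity of depression at entry (HAMD-17 "scores higher than 17 at baseline"). It gives no lower limit for mRS or NIHSS and no upper limit for BI.

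Section 2.14 compares the groups on these outcomes by logistic regression under intention to treat. It names no covariates for those models.

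**The concern.** A proportion improved should count people who got better. Under the mRS rule and the NIHSS 0–1 route it also counts people who entered at that level and stayed there, and even people who got worse within it. A reader of the results would take the figure in each arm as recovery when part of it is baseline status.

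The second cost is sensitivity. Participants already at the level add successes to both arms, so any effect on the others is averaged over people who cannot show it. BI ≥90 shares this cost, though not the labelling problem. With 70 participants there is little sensitivity to spare.

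**Working it through.** **1. What the rules do to a participant who does not improve**

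| Baseline → follow-up | Actual change | Outcome under 2.6.2 |
|---|---|---|
| mRS 2 → 2 | none | improved |
| mRS 0 → 2 | worse | improved |
| NIHSS 1 → 1 | none | improved (0–1 route) |
| NIHSS 0 → 1 | worse | improved (0–1 route) |
| BI 95 → 95 | none | meets ≥90 (not called improvement) |

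Section 2.3 excludes none of these baselines.

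**2. What the NIHSS 0–1 route adds to the reduction route**

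For a whole-number baseline b of 2 or more and a follow-up score of 0 or 1, the proportional reduction is at least (b − 1)/b. The smallest value is at b = 2: 1/2 = 50%. So everyone who reaches 0–1 from a baseline above 1 already qualifies by the reduction route. A move from 1 to 0 is a 100% reduction and qualifies too. The 0–1 route therefore adds only 0 → 0, 1 → 1 and 0 → 1, none of which is an improvement.

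**3. Contrast with the primary outcome**

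Section 2.6.1 also has a level route (HAMD-17 ≤7). Entry requires a score above 17, so the lowest eligible baseline is 18, and reaching 7 means a fall of at least 11/18 = 61%. Nobody can meet it unchanged. The functional outcomes have no such entry limit.

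**4. Dilution**

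The plan gives no expected rates for these outcomes (the sample size in 2.13 concerns HAMD-17 only) and no baseline distribution, so there is no stated figure to reproduce. The inputs below are assumptions, shown over a range.

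Let f be the share at the level at baseline, equal in both arms and staying there. Let a and b be the rates at which the others reach it in the active and sham arms. Then

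- active = f + (1 − f)a, sham = f + (1 − f)b
- visible difference = (1 − f)(a − b)

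With a = 20% and b = 10%:

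| f | Active | Sham | Visible difference |
|---|---|---|---|
| 0 | 20% | 10% | 10 points |
| 0.2 | 36% | 28% | 8 points |
| 0.4 | 52% | 46% | 6 points |
| 0.6 | 68% | 64% | 4 points |
| 0.8 | 84% | 82% | 2 points |

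For power, borrow the 50% versus 15% that 2.13 assumes for the primary outcome, purely as an illustration, with 35 per arm and a two-sided 5% test:

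| f | Active vs sham | Power, all participants | Power, only those not at the level |
|---|---|---|---|
| 0 | 50% vs 15% | 90% | 90% (35 per arm) |
| 0.2 | 60% vs 32% | 66% | 82% (28 per arm) |
| 0.4 | 70% vs 49% | 43% | 69% (21 per arm) |
| 0.6 | 80% vs 66% | 26% | 51% (14 per arm) |
| 0.8 | 90% vs 83% | 13% | 27% (7 per arm) |

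At f = 0.4, the share of counted successes who had not changed is 0.40/0.49 = 82% in the sham arm and 0.40/0.70 = 57% in the active arm.

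**The case against.** **The comparison is still valid.** A reader might infer that a chance baseline imbalance would be reported as a treatment effect, or that these outcomes measure only who was enrolled. The documents do not support that. Allocation is randomised 1:1 with a concealed schedule (2.9) and analysis is by intention to treat, so the difference in proportions at a level is unbiased, and chance imbalance is already covered by the 5% error. With 35 per arm and a true 60% in both, a gap of 10 points or more does arise in about 39% of trials, but that is not a false-positive rate: 23/35 versus 19/35 gives p = 0.33, and the unadjusted test rejects in 4.8% of trials. This objection stands in full.

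**BI is correctly labelled.** It is presented as status at follow-up. This stands; only the loss of sensitivity applies to it.

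**NIHSS has a real change criterion.** It does, and the fault is confined to the 0–1 route. But that route adds only people who did not improve.

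**The models may be adjusted.** A journal article often leaves covariates to the full protocol or analysis plan, so silence in 2.14 does not show that the models are unadjusted. This stands. It does not rescue the definitions, which 2.6.2 fixes: a covariate cannot turn mRS 0–2 into improvement.

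**The impact is unknown.** No figure shows how many participants will enter at these levels. This stands, and it is why only a range is given.

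**Conclusion.** The definitions are wrong as written for mRS and for the NIHSS 0–1 route: they record unchanged and some worsened participants as improved. This follows from 2.6.2 and 2.3 alone and needs no assumption beyond whole-number scores.

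The size cannot be fixed from the document. If those at the level stay there and the rest reach it at 20% versus 10%, the visible contrast falls from 10 points to between 8 and 2 as the baseline share rises from 20% to 80%. For BI the same dilution applies if many start at 90 or above, and baseline adjustment is an improvement there, not the correction of an error.

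No bias between arms and no inflated type I error follows. The primary outcome and the sample size are untouched. The point merits a change because it affects how secondary results will be read and the change is cheap.

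**What to change.** **In 2.6.2, choose one:**

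- Define improvement relative to baseline. mRS: reaching 0–2 from a baseline above 2. NIHSS: a reduction of at least 50%, or reaching 0–1 from a baseline above 1. The second NIHSS clause is implied by the first and may be dropped; a baseline of 0 should be stated as unable to improve.
- Or rename the outcomes as the proportion with mRS 0–2 and the proportion with NIHSS 0–1. For NIHSS the 50% reduction would then be reported separately.

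**In 2.14:** state that the mRS, NIHSS and BI models include the baseline score of the same scale, and that the number in each arm who met each threshold at baseline will be reported.

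**Cost:** wording only. Section 2.1 already provides for outcome assessment at baseline, so no visit or participant is added. The downside is a smaller denominator if the analysis is restricted to those outside the threshold at entry, for example 21 per arm instead of 35 if 40% start at the level. Renaming with baseline adjustment avoids that restriction, but the proportions then describe status and not recovery.

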### Adverse effects

2.7

Adverse events will be recorded on Case Report Forms (CRF) though the overall trial at weeks 4 and 8, according to vital signs, the treatment-emergent symptom scale (TESS) and EEG.

The proportions of participants who have symptoms in the TESS will be analyzed at weeks 4 and 8. TESS is composed of behavioral toxicity, laboratory abnormalities, nervous system, automatic nervous system, cardiovascular system and six other aspects (ranging from 0 to 4, the higher score, the more serious the adverse reactions).

The proportions of participants have an epileptic seizure based on EEG activity and clinical manifestations at weeks 4 and 8.^[52]^ At the request of the local ethics committee, EEG recordings will be monitored for each participant in the neurophysiology lab of the Department of Neurology of Xuanwu Hospital, Capital Medical University according to the electrode locations of the international 10/20 system for EEG recording at baseline and weeks 4 and 8. All participants will be recorded by EEG equipment for more than 30 minutes,^[29]^ and whether the participant will have an epileptic seizure will be assessed by EEG professional technicians and investigators.

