### Study visits and procedures

2.8

The visit schedule for all assessments (baseline, at weeks 4 and 8) is presented in Table 1. Participants will be evaluated by the two independent raters, who are blind to group assignment, at each observational timepoints. Baseline assessments, demographic characteristics, and medical history will be gathered at the first visit only. All concurrent medications will be recorded during the 4-week intervention period (i.e., baseline to week 4) and the another 4-week follow-up period (i.e., week 4 to week 8), including the name, dosage, and course of these medications. Primary and secondary outcomes and safety will be collected at weeks 4 and 8.

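### The TESS safety outcome counts participants with symptoms at weeks 4 and 8 without requiring that a symptom be new or worse than before the first session

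*Protocol article*

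**What the plan says.** Section 2.7 (Adverse effects) names the instrument, "the treatment-emergent symptom scale (TESS) and EEG", alongside vital signs as the basis for recording adverse events. On timing it says: "Adverse events will be recorded on Case Report Forms (CRF) though the overall trial at weeks 4 and 8". The outcome itself is: "The proportions of participants who have symptoms in the TESS will be analyzed at weeks 4 and 8". The scale is described as covering behavioral toxicity, laboratory abnormalities, the nervous, autonomic and cardiovascular systems and other aspects, "ranging from 0 to 4, the higher score, the more serious the adverse reactions".

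For the safety EEG, the same section does name a baseline: "electrode locations of the international 10/20 system for EEG recording at baseline and weeks 4 and 8".

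Section 2.8 (Study visits and procedures) adds: "Primary and secondary outcomes and safety will be collected at weeks 4 and 8". It also says: "The visit schedule for all assessments (baseline, at weeks 4 and 8) is presented in Table 1". The content of Table 1 is not shown in the text available.

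Section 2.3 (Inclusion and exclusion criteria) requires "having the Hamilton Depression Rating Scale 17-Item (HAMD-17) scores higher than 17 at baseline" and more than 6 months since stroke onset. Section 2.5 lets routine antiplatelet, lipid-lowering, antihypertensive or antidiabetic therapy continue.

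**The concern.** The TESS outcome, as written, is the prevalence of symptoms at each of two visits. It is not the incidence of symptoms that arise or worsen under treatment. The population is depressed and post-stroke, many may take vascular or antidiabetic drugs, and the listed TESS domains overlap with those conditions. Some participants can therefore be expected to have symptoms in these domains before the first session, and nothing in the stated rule keeps those symptoms out of the count.

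Two things follow if the rule is applied literally. First, the reported proportions are higher in both arms than the proportions with new problems. Second, a participant who already has a symptom cannot add to the count by developing another, so a real excess in the active arm is diluted. Safety is a stated aim of the trial, and a diluted comparison makes it easier to report no difference when there is one.

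**Working it through.** The document gives no TESS rate, so there is no figure of the plan's own to reproduce on this point. The check has a textual part and an illustrative part.

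**1. How outcomes are tied to baseline**

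| Outcome | Section | Tied to baseline in the stated definition? |
|---|---|---|
| HAMD-17 response | 2.6.1 | Yes: reduction of at least 50% from baseline (or a score of 7 or less) |
| NIHSS improvement | 2.6.2 | Yes in part: reduction of at least 50%, or a total of 0–1 |
| HAMA, MMSE, MoCA, oscillations | 2.6.2 | Yes: stated as changes |
| mRS, BI | 2.6.2 | No: fixed thresholds |
| Safety EEG | 2.7 | Baseline recording named |
| TESS | 2.7 | No |

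The article thus refers several outcomes to baseline, but does not do so for TESS.

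**2. Size of the dilution (all rates assumed)**

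Let p be the share in each arm with a TESS symptom at baseline that persists and is scored, and r the rate of truly new symptoms, independent of p. Under the stated rule:

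observed proportion = p + (1 − p) × r

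observed difference = (1 − p) × (r active − r sham)

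Take r = 25% active and 10% sham, a true excess of 15 points.

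| p | Active | Sham | Difference |
|---|---|---|---|
| 0% | 25% | 10% | 15 points |
| 30% | 0.30 + 0.70 × 0.25 = 47.5% | 0.30 + 0.70 × 0.10 = 37% | 10.5 points |
| 60% | 0.60 + 0.40 × 0.25 = 70% | 0.60 + 0.40 × 0.10 = 64% | 6 points |
| 80% | 0.80 + 0.20 × 0.25 = 85% | 0.80 + 0.20 × 0.10 = 82% | 3 points |

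**3. Effect on power (assumed rates; 35 per arm, half of the planned 70)**

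This uses a two-sided 5% normal-approximation test and a larger assumed excess of 40% v 10%, so that the undiluted comparison starts with reasonable power.

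| p | Active v sham | Difference | Power |
|---|---|---|---|
| 0% | 40% v 10% | 30 points | 84% |
| 30% | 58% v 37% | 21 points | 42% |
| 50% | 70% v 55% | 15 points | 25% |
| 70% | 82% v 73% | 9 points | 14% |

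At 25% v 10%, power is only about 38% even with p = 0.

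**4. If treatment relieves baseline symptoms**

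Section 2.13 assumes improvement in 50% of the active arm and 15% of the sham arm at 8 weeks. Assume also p = 60%, that half of those participants have TESS symptoms due to depression, and that these symptoms resolve in improvers.

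- Persisting, active: 0.60 × (1 − 0.5 × 0.50) = 45%.
- Persisting, sham: 0.60 × (1 − 0.5 × 0.15) = 55.5%.
- Observed, active: 0.45 + 0.55 × 0.25 = 58.75%.
- Observed, sham: 0.555 + 0.445 × 0.10 = 59.95%.

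Under these assumptions a true 15-point excess would read as about 1 point in favour of active. This holds only if TESS scores depressive symptoms as such. The article lists domains, not items, so it does not settle that.

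**The case against.** A reader might go further and infer that TESS is collected at weeks 4 and 8 only, that pre-existing symptoms are in fact counted as treatment-emergent, and that the outcome therefore measures disease burden. The document does not support any of these.

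- **Baseline collection.** The section 2.8 sentence that gives weeks 4 and 8 for safety also covers the primary and secondary outcomes, and HAMD-17 plainly has a baseline value. The sentence therefore cannot show that a baseline TESS is absent. Section 2.1 has outcomes evaluated at baseline as well, section 2.11 has case report forms completed at baseline, and Table 1 is not shown.
- **What raters will count.** The scale is called treatment-emergent and its score is said to grade adverse reactions. Raters may leave out symptoms that were there before. No section says that prior symptoms are counted, and none says that they are excluded.
- **Direction.** With randomisation and a sham control, background symptoms at entry would not be expected to favour one arm. The expected effect is higher rates in both arms and a smaller contrast. Any difference by arm needs the further assumption in step 4 of the working.
- **Size.** Every rate is assumed, and section 2.3 excludes severe or unstable organic disease, so a high p is not established. At 25% v 10% the comparison has low power even without background symptoms, so a baseline rule would not by itself make it conclusive.
- **Condensed article.** Rating instructions may sit in the full protocol or analysis plan.

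These points stand against the stronger readings. They do not remove the narrower one: section 2.7 states a counting rule, and that rule has no baseline reference. The name of a scale is not a counting rule. If no baseline rating is taken, the analysis plan cannot recover it later.

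**Conclusion.** The point holds in its limited form. The stated TESS outcome is the proportion with symptoms at each of weeks 4 and 8, with no condition that a symptom be new or worse. Followed as written, it can count symptoms present at entry, raise both arms' proportions and dilute a real excess by the factor (1 − p). On assumed rates of 25% v 10%, that takes 15 points to 10.5 at p = 30% and to 6 at p = 60%. This rests on baseline symptoms being scored and persisting, and on new symptoms being independent of them; the document supplies none of these rates. A further shrinkage through symptom relief is possible but depends on what TESS items score. Whether a baseline TESS exists is open. Severity is low to moderate: this is a safety outcome, not the primary analysis, and vital signs and seizures are assessed as well.

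**What to change.** 1. Confirm that TESS is rated at baseline before the first session. If it is not, add it to the existing baseline visit and say so in sections 2.7 and 2.8.
2. Redefine the outcome in section 2.7 as the proportion of participants with at least one TESS item that is new or scored higher than at baseline, by week 4 and by week 8.
3. List symptoms already present at baseline separately, by arm.

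The cost is at most one more checklist at a visit that already takes place, a one-sentence change to the definition, and a little more analysis work. The sample size and the primary analysis are not affected.

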### Study visits and procedures

2.8

The visit schedule for all assessments (baseline, at weeks 4 and 8) is presented in Table 1. Participants will be evaluated by the two independent raters, who are blind to group assignment, at each observational timepoints. Baseline assessments, demographic characteristics, and medical history will be gathered at the first visit only. All concurrent medications will be recorded during the 4-week intervention period (i.e., baseline to week 4) and the another 4-week follow-up period (i.e., week 4 to week 8), including the name, dosage, and course of these medications. Primary and secondary outcomes and safety will be collected at weeks 4 and 8.

**Table 1 T1:**
[figure not shown]
Schedule of the enrollment, interventions, and assessments in the trial.

### Randomization and blinding

2.9

An independent statistician, who is not be involved with the enrolment nor the assessment of the study participants, will establish and keep the concealed randomization schedule using a computer-generated random number sequence. The randomization sequence will be computed with the blocks of 4. Participants will be randomized into 2 groups with a ratio of 1:1, and the active and sham groups will be coded A and B, respectively. The code will be set in an opaque envelope and subsequently sealed. 10 tACS devices (5 sham and 5 active) have the same size, color, appearance, weight, and odor, and are coded as A or B. If one participant is allotted to A, only devices coded as A will be used through the course of the intervention, similarly if B, only B devices can be utilized. Two trained nurses of tACS devices will know the tACS devices’ status, but not involved in the assessment of participants and will keep blindness to participants and other study staff about tACS devices. Persons involving in the study, including the investigators, raters, EEG technicians, participants, trial monitors, and statistician, will be blinded to treatment assignment during double-blinded treatment until the end of follow-up.

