### Study design

2.1

This is an 8-week, randomized controlled trial (RCT) aimed to evaluate the efficacy of tACS in treating PSD. Seventy participants with PSD will be recruited from the Department of Neurology, Xuanwu Hospital of Capital Medical University, Beijing, China. After obtaining written informed consent from participants, potential participants will be screened for their eligibility. If eligible, they will be randomized to either the active or sham intervention group with a ratio of 1:1. Participants will undergo a 4-week intervention period (week 4), and another 4-week observational follow up (week 8). Outcomes will be evaluated for all participants at 3 time points: at baseline, at week 4, and week 8. All procedures of this trial will follow the strictly Consolidated Standards of Reporting Trials (CONSORT) guidelines (see Fig. 1) and Standard Protocol Items: Recommendations for Interventional Trials (SPIRIT) Checklist.

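### A fixed, disclosed block size of 4 and two shared device letters at one centre leave an avoidable opening for predicting the next allocation

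*Protocol article*

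**What the plan says.** Section 2.9 (Randomization and blinding) gives one constant block size: "The randomization sequence will be computed with the blocks of 4". On the ratio and the codes it says: "Participants will be randomized into 2 groups with a ratio of 1:1, and the active and sham groups will be coded A and B, respectively". Device labels use the same two codes: "10 tACS devices (5 sham and 5 active) have the same size, color, appearance, weight, and odor, and are coded as A or B". The letter does not change for a given participant: "If one participant is allotted to A, only devices coded as A will be used through the course of the intervention". Section 2.5 gives 20 sessions per participant, delivered by two trained nurses.

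On who knows what, section 2.9 states: "Two trained nurses of tACS devices will know the tACS devices’ status, but not involved in the assessment of participants". The same sentence requires the nurses to keep this from participants and other study staff. Investigators and raters are listed among those blinded until follow-up ends. The list is held by an independent statistician, separate from both enrolment and assessment, who "will establish and keep the concealed randomization schedule using a computer-generated random number sequence". Codes go into sealed opaque envelopes.

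Section 2.1 places recruitment in one department: "Seventy participants with PSD will be recruited from the Department of Neurology". Under section 2.2 a trial investigator judges eligibility. The exclusion criteria in section 2.3 end with an open clause: "any situations the investigators believe that they are not suitable for this study".

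**The concern.** Concealment has two parts: nobody may read the next assignment, and nobody may work it out. The article deals with the first. On the second, it fixes a small block, discloses its size, runs it at one department where all earlier allocations accumulate, and marks each treated participant with one of two letters. A person who keeps count of the letters needs no envelope. If the first three participants of a block were treated on A, A and B, the fourth will be B.

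This matters if such knowledge reaches someone who can influence entry. Eligibility includes an open-ended judgement, so a candidate could be enrolled, deferred or excluded with the coming arm in mind. The primary outcome is a binary response in 70 participants, where steering a few candidates can matter. Selection before randomization is not repaired by an intention-to-treat analysis. The blinding check in section 2.10 would not reveal it either, because it asks about treatment already received and not about the next allocation.

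**Working it through.** The article gives no figure for predictability, so there is none to reproduce.

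**Inputs.** Block size 4, ratio 1:1 and two letters (section 2.9); one centre (sections 2.1 and 3); total 70 (section 2.13). *Assumption:* the observer knows the block size and sees every earlier letter in order.

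**Orders.** A block of two A and two B has 4!/(2!·2!) = 6 equally likely orders. An allocation is certain once one letter is used up. The best guess is the letter with more places left.

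| Position in block | Probability that it is certain | Probability that the best guess is right |
|---|---|---|
| 1 | 0 | 1/2 |
| 2 | 0 | 2/3 |
| 3 | 1/3 (first two letters alike) | 1/3 × 1 + 2/3 × 1/2 = 2/3 |
| 4 | 1 | 1 |
| Sum | 1.333 | 2.833 |

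**Per full block.** Certain: 1.333/4 = 33.3%. Best guess right: 2.833/4 = 70.8%.

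**Over 70 participants.** 70 = 17 × 4 + 2, so there are 17 full blocks and two places of an eighteenth.
- Certain: 17 × 1.333 + 0 = 22.7, and 22.7/70 = 32.4%.
- Best guess right: 17 × 2.833 + 1/2 + 2/3 = 49.3, and 49.3/70 = 70.5%.

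**Range.** These figures are a ceiling. For someone who sees no letters, nothing is certain and the guess is right 50% of the time.

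**Effect of varying the block size.** These are simulations of 70 participants, with block sizes equally likely and an observer who sees all earlier letters and knows which sizes are possible.

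| Block sizes | Certain | Best guess right |
|---|---|---|
| 4, fixed | 32.4% | 70.5% |
| 4 and 6 | about 6% (0.056 × 70 = 3.9 participants) | about 69% |
| 2, 4 and 6 | about 4% (0.04 × 70 = 2.8 participants) | about 70% |

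The guessing rate can be checked by hand. A fixed block of 6 gives 68.3%, or 4.1 of 6. An equal mix of 4 and 6 therefore gives (2.833 + 4.1)/10 = 69.3% over complete blocks, which agrees with the simulation. The rate hardly moves because guessing the arm with fewer participants so far needs no knowledge of any block size.

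**The case against.** The strongest reply is that the article puts knowledge of the codes and discretion over entry in different hands. Two nurses treat and know device status. A trial investigator judges eligibility, and investigators are listed as blinded. The nurses must keep device status from other staff. Nothing in the text puts an investigator at a treatment session, shows an investigator a device letter, or gives the nurses a part in screening. The schedule is held independently and the envelopes are opaque and sealed.

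Most of this stands. A reader might infer that enrolling staff see the earlier letters, or that a third of allocations will in fact be foreseen. The documents do not support either reading. The one-third figure applies only to someone who follows all letters in order. The nurses are in a position to do so; for investigators it would be an inference.

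Two things do not fall to this reply. First, the safeguards protect the next envelope and the nurses' knowledge of device status, but none expressly hides the letters already in use, and the meaning of the letters is printed in the article. Second, the statistician is separated from enrolment and assessment, whereas the nurses are expressly separated from assessment only.

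Two further inferences should be left aside. The article names no stratification factor and does not describe release of envelopes in numbered order, but a condensed article commonly leaves such details to the full protocol. The open exclusion clause is not a defect in itself; it matters here only as the point where foreknowledge could be used.

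**Conclusion.** The point holds as an avoidable weakness in the stated design. Its size is at most about 32% of allocations certain (about 23 of 70) and about 70% guessed correctly, for an observer who knows the block size and follows every earlier letter in order. It rests on the fixed and disclosed block of 4, the single centre and the two shared letters, all of which are stated. It also rests on the possibility that letters become known to someone with influence on entry, which the text neither shows nor fully closes off. It should be corrected because the remedy is cheap. It is no ground for saying that the trial's results will be biased.

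**What to change.** Change section 2.9 in two ways, because neither is enough alone.

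1. **Block sizes.** Generate the list with randomly varying block sizes, for example 4 and 6. Keep the sizes out of the protocol and all site documents until database lock. This removes most of the certain allocations.
2. **Letters and roles.** State that the nurses take no part in screening or enrolment and that device letters are not shown to enrolling staff. Alternatively, replace the two shared letters with participant-specific or multiple device codes. This addresses the guessing rate, which varying the blocks leaves almost unchanged.

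**Cost.** One change to the program that generates the list, a few sentences in section 2.9, and minor relabelling if new device codes are chosen. The arms could differ by up to three if recruitment stops halfway through a block of 6, against two halfway through a block of 4. If recruitment stops at exactly 70, an even number of places is filled in the last block and the largest difference is two under either scheme (2 to 0, or 3 to 1 after four places of a block of 6).
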